#### Ethics approval and consent to participate

Research ethic committee approval was obtained (approval number: 22/LO/0292). Written, informed consent to participate will be obtained from all participants. The Chief Investigator (CI), or person to whom the CI delegates the responsibility will obtain written informed consent from each parent/legal guardian. All trial investigators seeking consent must also receive Human Tissue Act training for the taking of consent involving tissues and cells used as part of the trial and be up-to-date with their Good Clinical Practice training. Model consent form and other related documentation given to participants and authorized surrogates will be provided on request. Additional 1ml of blood will be taken for research assays at the same time as clinical blood tests. Consent for research blood samples will be optional.

#### Intervention

*HMB002 production*. The final investigational product will be made of:

primary human hepatocytes isolated from donor organs, procured through NHSBT after specific consent for liver cell isolation, in the NIHR/Welcome Trust Cell Therapy Unit at King’s College Hospital (Licence Number 11062)MSCs procured after consent and isolated in King’s College Hospital GMP Cell Therapy Unit above.a modified alginate produced under GMP regulations.transplant medium (CMRL-1066 with Human Albumin Solution).

The final product is named as HMB002. The alginate microbeads will be manufactured in a GMP unit, from cells isolated/prepared and cryopreserved following EU-GMP regulation. The final product is packaged as 20mL/kg final volume in sterile syringes for infusion, once quality control checks are satisfactory. Children who weigh in excess of 33kg cannot be treated within the study due to current capacity for HMB002 manufacture. Children with a known allergy to gentamicin will also be excluded from the trial as the MSCs are manufactured using gentamicin. The donation, procurement and testing of the human tissues and cells are in conformity with the relevant regulations. The donation of the human cells used to manufacture the IMP is not considered a part of this trial.

*IMP packaging and storage*. The final product (HMB002) is packed in sterile syringes and kept at 2–8°C from time of manufacture to administration. The IMP will be administered shortly after production and always within 8 hours from time of manufacture. Release criteria for the final product include checks of sterility, bead characteristics, endotoxinemia and mycoplasma testing. The treating physician will be informed if the product fails any of the final release tests.

*Dosing regimen*. The route of administration of the product is intra-peritoneal with a 14-16G cannula under ultrasound guidance by a physician. A single dose (weight-dependent) will be used in all patients. There are no increments of dosage. The dose will be administered as soon as possible following parental/legal guardian consent and screening of the patient, as these patients are critically ill. The infusion will be administered at a rate of approximately 150-200ml per hour under antibiotic prophylaxis and close monitoring. This dose has been determined using in vitro, in vivo and previous clinical pilot experience. An infusion of more than 80% of the final product for the patient will be considered as a completed infusion.

#### Criteria for discontinuing or modifying interventions

Where possible intra-abdominal pressure will be measured pre-infusion using urinary catheter. Pre-infusion Checks form will be completed prior to dosing with HMB002.

Pre-infusion checks include:

i. Correction of coagulopathyii. Haemoglobin > 7g/dliii. Patient has not got tense ascitesiv. Patient is sufficiently stable to tolerate procedurev. Patient diagnosis / status has not changed from time of screening and consentvi. No organ transplant is available.vii. Full PICU / NICU / HDU monitoring in place and staffing sufficient to provide the same monitoring following the infusion.

Whenever the pre-infusion checks reveal that the patient is not suitable for infusion, the procedure is delayed or abandoned. The patient may be scheduled for infusion on a different day if the patient is still eligible and does not have any contraindications for infusion.

#### Outcomes

*Primary endpoints*.

Safety: Moderate to severe (including life threatening and death) adverse event occurrences due to product in 1^st^ 52 weeks post procedureTolerability: assessed by the proportion of initiated infusions where >80% of the infusion is received by the patient.Biological activity: Survival with native liver at 24 weeks post treatment.

*Secondary endpoints*.

Change in blood marker levels including haematological, biochemical and coagulationbaseline to 52 weeks post treatment.Quality of life measuresPatient survival with native liver at 52 weeks post treatmentPatient survival with transplanted or native liver at 24- and 52-weeks post treatment.

*Exploratory end points*

To assess the assay ‘Hepamorph’ which distinguishes the recipient liver cell derived proteins from the donor liver cell derived proteins using a targeted mass spectrometry approach.To analyse viability and function of microbeads which are retrieved from the intraperitoneal cavity either at laparoscopy or transplant for phenotype ex vivo.

#### Participant timeline

The participant timeline is detailed in Fig 3. The schedule of assessment has been explained in Fig 1.

**Fig 3 pone.0288185.g003:**
[figure not shown]
Participant timeline flowchart.

Safety monitoring will be until 10 years after HMB002 infusion. This will be aligned with routine care. Routine follow up will be conducted annually as a minimum but may be more frequent should the clinical condition of the child or young person require this. For example, if the child has undergone liver transplantation, follow up will be frequent and lifelong.

#### Adverse event reporting and harms

*Specification*, *timing*, *definitions and recording of safety parameters*. *Definitions*. The Medicines for Human Use (Clinical Trials) Regulations 2004 and Amended Regulations 2006 defines Adverse Event (AE), Adverse Reaction (AR), Unexpected Adverse Reaction (UAR), Serious adverse Event (SAE), Serious Adverse Reaction (SAR) and Suspected Unexpected Serious Adverse Reaction (SUSAR).

Documentation of the AEs in the eCRF will be according to the following criteria:

Description of the AE: diagnosis if known, with signs and symptoms, giving details appropriate to the event,Dates of onset and resolution of the AE,Severity, grading–using the NCI Common Terminology Criteria for Adverse Events (CTCAE, version 4.0) and detailed below. If not included in CTCAE, this will be a clinical decision and graded as detailed below in severity of adverse events section.
Assessment of causal relationship to study treatment (category—definitely, probably, possibly, unlikely, unrelated)Action taken regarding study treatment: none / infusion discontinued / infusion delayedOutcome: complete recovery/not yet recovered/recovered with sequelae/death/unknown. The investigator may be asked to provide follow-up information and/or discharge summaries as needed.

The assignment of causality should be made by the investigator responsible for the care of the participant and discussed with the Chief Investigator (CI) in cases where causality is doubtful.

Safety parameters and adverse event (AE, SAE, SAR and SUSAR) information will be collected from the point of parent/legal guardian consent until week 52 post IMP administration. During the infusion and for at least 24 hours afterwards the patient will be continuously monitored in PICU / NICU / HDU. Intra-abdominal pressure will be monitored via the bladder if possible. Safety will be assessed using history of symptoms which have occurred or worsened since study commencement, physical examination, blood tests including white cell count, haemoglobin, platelets, Urea and electrolytes, liver function tests, lactate, venous blood gas. While an inpatient, need for intervention and escalation of care will also be recorded. Ultrasound may be used to assess for intra-abdominal bleeding.

During long term follow up (post week 52 visit), AEs and SAES will be documented in the medical notes as per routine care practise and reviewed by clinicians. However, only SAEs, SARs and SUSARS will be reported (excluding known complications following liver transplant). Any serious adverse events that are deemed related to the IMP will be considered unexpected (SUSARs). All liver transplants will be reported as an SAE. However, known complications which are universal in patients post liver transplant will not be reported as SAEs to the sponsor, unless they result in death, are considered to be related to the study drug or worse than what would normally be expected.

#### Relevant concomitant care permitted or prohibited during the trial

There are no special dietary or other requirements from the participants. They will have standard of care treatment and monitoring involving adherence to standard treatment regime and receive immunosuppressive treatment in the case of liver transplantation. Data will be collected relating to concomitant medications at every study visit.

#### Provisions for post-trial care

There will be no additional post-trial care apart from what is clinically indicated. No compensation is planned for those who suffer from complications due to trial participation except for what may arise from clinical negligence. As the sponsor, King’s College Hospital NHS Foundation Trust have clinical negligence cover as part of the NHS Clinical Negligence Scheme for Trusts.

#### Recruitment and trial status

Recruitment is yet to begin and the trial is expected to finish recruitment in 3 years. This trial will be communicated within the Pediatric hepatology and intensive care units which makes healthcare providers aware of the study and to encourage recruitment.

#### Data collection and management

*Plans for assessment and collection of outcomes*. Source documentation for the study includes, but is not limited to informed consent forms, medical records, clinical reports, laboratory reports, hospital correspondence and quality of life questionnaires. The validated PedsQL forms used in the study are PedsQL Parent (13–18 years) version 4.0, PedsQL Infant(1-12months) version 1.0, PedsQL Infant(13-24months) version 1.0, PedsQL Parent (2–4 years) version 4.0, PedsQL 5–7 Years version 4.0, PedsQL Parent (5–7 years) version 4.0, PedsQL 8–12 Years version 4.0, PedsQL Parent (8–12 years) version 4.0 and PedsQL 13–18 Years version 4.0.

*Plans to promote participant retention and complete follow-up*. Participants have the right to withdraw from the study at any time for any reason. Should a patient decide to withdraw from study, efforts will be made to explain the importance of remaining on trial follow up and seek permission to continue to allow routine follow-up data to be used for trial purposes (with parent / legal guardian consent). Patients who undergo liver transplant following IMP administration during the study period will not be withdrawn from the study but will continue to undergo monitoring and data collection.

*Data management*. A web based electronic data capture system will be designed, using the InferMed Macro 4 system. It will be hosted at a dedicated secure server within King’s college London. A full audit trial of data entry and any changes to data will be available. Over the course of the trial, the trial monitor will conduct on-site monitoring. The data entered into an electronic form should be verifiable with original source records kept at study centre. Following completion of monitoring and data cleaning of all week-52 post IMP visit data, the site PI will review all the data for each participant and provide electronic sign-off to verify that all the data are complete and correct. At this point, all data will be formally locked for analysis. Safety monitoring data collected during the long term follow up period (week 52 to 10 years post IMP) will be recorded on a separate database and locked following PI review and sign off.

At the end of the trial, all essential documentation will be archived for a minimum of 30 years in a GCP compliant archive facility. The documents that relate to IMP traceability will be retained for a minimum of 30 years and beyond the expiry date of the product.

*Confidentiality*. Patient data will be pseudo-anonymised. All trial data will be stored in line with the Medicines for Humans Use (Clinical Trials) Amended regulations 2006, the Data protection Act 2018 and GDPR.

*Plans for collection*, *laboratory evaluation and storage of biological specimens for genetic or molecular analysis in this trial/future use*. Plasma samples will be collected for HepaMorph panel and Inflammasome tests (proprietary tests in validation). Any surplus plasma sample will be transferred to King’s College Hospital Pediatric liver biobank for long term storage (HTA License no: 12378), following consent from parent/legal guardian.

#### Statistical methods

*Analysis of primary endpoints*.

The number of moderate to severe adverse event occurrences due to product in 1^st^ 52 weeks post procedure will be reported.The proportion of initiated infusions where >80% of the infusion is received by the patient will be reporter.Survival with native liver at 24 weeks post treatment and 95% confidence interval will be reported as one minus the cumulative incidence of death with native liver, liver transplant being considered as competing events.

*Analysis of secondary endpoints*.

Change in blood marker levels (haematological, biochemical and coagulation) will be reported from baseline to 52 weeks post-treatment.Change in quality-of-life measures levels will be reported from baseline to 52 weeks post treatment.Survival with native liver at 52 weeks post treatment and 95% confidence interval will be reported as one minus the cumulative incidence of death with native liver, liver transplant being considered as competing events.Overall survival and 95% confidence interval at 24 weeks and 52 weeks post treatment will be estimated using the Kaplan-Meier method.

*Other reporting*.

A comprehensive report of the collected examination items will be provided according to the protocol’s schedule of assessment.

An analysis of outcomes will be conducted at stage 1 Go/No Go time point for DSMB safety review, when the 9^th^ patient has completed their 24-week post IMP study follow up.

According to the trial design, a first analysis will be conducted once 9 patients have received the proposed treatment and completed 24 weeks of follow up. If two or fewer survive with the native liver at 24 weeks after treatment then the trial will be stopped at this stage. Once 52-week follow up is completed for all 9 patients, primary and secondary endpoint will be analysed according to the protocol specification. If more than 2 survive with the native liver at 24 weeks after treatment, then recruitment will continue to a total of 17 patients (stage 2). Once 52 week follow up will be completed for all 17 patients having received the treatment, primary and secondary endpoints will be analysed according to the protocol specification.

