**Methods:**

A single centre, non-randomised, open-label, single-arm Simon’s two stage study will be conducted to evaluate the safety, biological activity and tolerability of transplantation of a single intraperitoneal dose of microbeads made from an optimum combination of a modified alginate, MSCs and hepatocytes in 17 patients less than 16 years of age with acute liver failure (Stage 1: 9 patients and Stage 2: 8 patient). Safety will be assessed by documenting moderate to severe (including life threatening and death) adverse events due to HMB002 in the first 52 weeks post-procedure. Tolerability will be assessed by observing the proportion of initiated infusions where >80% of infusion is received by the patient. Biological activity will be reflected in patient survival with native liver at 24 weeks post treatment.

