## Materials and methods

### Trial objectives

The trial objective is to evaluate if HMB002 is a safe and effective form of liver support in Pediatric acute liver failure to bridge the patient to native liver survival or liver transplantation. This study will involve intraperitoneal infusion of HMB002. The exact formulation of HMB002 is proprietary but the infusate will consist of alginate beads suspended in transplant medium (1:1 v/v). This is given as a single infusion under ultrasound guidance while observing for any adverse events related to increase in intrabdominal pressure. This will be in addition to standard of care in Pediatric acute liver failure. The beads will be removed using laparoscopy prior to discharge of the patient from hospital, or at time of transplantation, to minimize or eliminate the risk of adhesions within the peritoneal cavity.

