#### Primary objective

To evaluate the safety, biological activity and tolerability of transplantation of a single dose of microbeads made from optimum combination of modified alginate, MSCs and hepatocytes to Pediatric patients with acute liver failure.

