## Discussion

Our previous alginate encapsulation technique used PRONOVA^™^ UP, an ultrapure alginate that satisfied GMP standards. We had optimised the alginate percentage, cell density and bead size allowing the best cell survival, and demonstrated that this alginate was not immunogenic using in vitro tests [7]. However, this alginate led to limited in vitro cell survival. The development of HMB002 followed the hypothesis that co-encapsulation of hepatocytes with MSCs, in modified alginate microbeads, would substantially improve the survival and function of hepatocytes and be a feasible and effective form of cellular therapy for acute liver failure [5, 6].

This trial, while demonstrating the safety of HMB002 would support the design of a larger study if the intervention is found to be safe. The trial will also report 52-week survival outcome. This is not anticipated to change from 24-week outcome as this trial is to attempt to rescue acute liver failure. If the 52-week outcome differs from the 24-week outcome this observation will be an important consideration in the design of any future trial. The target population is too small and too unwell to do any significant dose escalation study.

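### The primary safety result is an occurrence count limited to product-caused events, which is narrower than the stated objective and need not include harm from the trial-required bead retrieval

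*Protocol article*

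**What the plan says.** The restriction to product-caused events appears in three places in the protocol article. The abstract (Methods) speaks of "adverse events due to HMB002 in the first 52 weeks post-procedure". The Outcomes section defines the primary safety endpoint as "Moderate to severe (including life threatening and death) adverse event occurrences due to product". Statistical methods then gives the summary: "The number of moderate to severe adverse event occurrences due to product".

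The Primary objective is wider: "To evaluate the safety, biological activity and tolerability of transplantation of a single dose of microbeads". The intervention has two invasive steps. The infusion is "intra-peritoneal with a 14-16G cannula under ultrasound guidance by a physician" (Intervention, dosing regimen). Retrieval is set out under Trial objectives: "The beads will be removed using laparoscopy prior to discharge of the patient from hospital, or at time of transplantation". The notes to Fig 1 add that the beads come out within 24 weeks in any case.

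Causality is recorded on five levels: "Assessment of causal relationship to study treatment (category—definitely, probably, possibly, unlikely, unrelated" (Adverse event reporting and harms). The article does not say which levels make an event product-caused, and it lists no separate relation to the infusion procedure or to retrieval.

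**The concern.** For a child who recovers without a transplant, the laparoscopy is done only because beads were infused. A complication of it is harm from taking part in the transplantation, yet it is not naturally described as caused by the product. An investigator who applies the endpoint literally would leave it out. A cannula bleed could go either way.

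The trial has one arm, is open label and treats critically ill children. Attribution is made by the investigator responsible for the child's care, with doubtful cases discussed with the Chief Investigator. A result that rests wholly on attribution, with no stated cut-off on the scale, is hard to interpret and hard to carry into the larger trial that this study is meant to inform. Counting occurrences adds a second difficulty, because the number of children harmed cannot be recovered from the count.

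**Working it through.** **The plan's own figures.** No numerical target is stated for safety. The only design figures are those of the Simon design under Sample size: stop at 2 or fewer of 9, success at 7 or more of 17, response rates 0.20 and 0.50. The rejection probability is the sum over x = 3 to 9 of P(X1 = x | 9, p) × P(X2 ≥ 7 − x | 8, p).

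- At p = 0.20 it is 0.034, within the 5% limit.
- At p = 0.50 it is 0.806, above the 80% target.
- The probability of stopping after 9 children is 0.738 at p = 0.20 and 0.090 at p = 0.50.

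The design reproduces and is not affected by this point. It does show that a safety result based on 9 children is a realistic outcome.

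**Which harms enter the primary count, as worded.**

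- Reaction to the beads: enters.
- Injury from the cannula infusion: unclear. The endpoint refers to the product, while the causality scale refers to study treatment, which could include the infusion.
- Injury from the retrieval laparoscopy: need not enter.

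**How many children are exposed to retrieval by laparoscopy.** A child alive with the native liver at 24 weeks has had no transplant at which the beads could be washed out, and retrieval is due by 24 weeks. If the trial meets its own success criterion, at least 7 of 17 children (7/17 = 41%) should therefore have had the laparoscopy. The successes of the trial are the children exposed to this harm. Retrieval falls inside the 52-week safety window.

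**What an occurrence count leaves open.** The event numbers here are assumptions for illustration, with exact (Clopper-Pearson) two-sided 95% intervals. Six occurrences are compatible with:

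- one child: 1/17 = 5.9% (0.1% to 28.7%);
- six children: 6/17 = 35.3% (14.2% to 61.7%).

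**What a zero count can exclude.** The two-sided 95% upper limit for 0 of n is 1 − 0.025^(1/n).

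- n = 17: 1 − 0.025^(1/17) = 19.5% (one-sided, with 0.05 in place of 0.025: 16.2%).
- n = 9: 1 − 0.025^(1/9) = 33.6% (one-sided: 28.3%).

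The chance of seeing at least one affected child among 17 is 1 − (1 − p)^17, which is 58% at a true risk of 5% and 83% at 10%.

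**Denominator.** Replacement of subjects allows children who do not tolerate the procedure to be replaced. The missing-data paragraph discards children with incomplete data. Neither rule says that such children stay in the safety analysis. Tolerability, by contrast, is already defined over initiated infusions.

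**The case against.** The strongest reply is that nothing is lost. Adverse events of any cause are collected from consent to week 52 with grade and causality. Infusion-site checks, intra-abdominal pressure and ultrasound for bleeding are planned. Failure to complete the infusion has its own primary endpoint, and deaths from any cause enter overall survival. The DSMB reviews data on individual children and can meet over any safety concern. All of this stands. A reader might infer that procedural harm goes unrecorded or is deliberately excluded, and the documents do not support that. It can only fall outside the primary safety result. The recruitment-halt triggers are also worded around reactions to the product, but the DSMB's general power to meet remains.

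Second, study treatment may well cover the infusion, since the recorded actions include stopping or delaying it. This too stands: exclusion of infusion harm is possible but not established. The reading for laparoscopy is firmer.

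Third, intervals and patient-level tables are often left to an analysis plan, which is not shown here. The missing interval alone would therefore not be a finding. However, the same list gives a proportion for tolerability and a 95% interval for native-liver survival, and only a number for safety.

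Fourth, the Discussion says "This trial, while demonstrating the safety of HMB002 would support the design of a larger study", which might be read as a safety claim made in advance. The sentence goes on to make this conditional on the intervention being found safe, so that reading fails.

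Finally, the limits of 19.5% and 33.6% come from the sample size and would be the same under any endpoint wording. They bear on how the conclusion is phrased and do not measure the attribution gap.

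**Conclusion.** The point holds in a limited form. The primary safety endpoint is narrower than the objective that it serves. Harm from the required retrieval laparoscopy, and possibly from the infusion, need not appear in it, and an occurrence count does not give the risk per child. No stated number is wrong and no decision rule depends on the safety count.

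The size of the attribution gap cannot be calculated, because the article gives no expected rate of procedural harm. What can be said is that at least 7 of 17 children would be exposed to the laparoscopy if the trial succeeds, assuming that the retrieval plan is followed. A zero count would still be compatible with a true risk of up to 19.5% in 17 children, or 33.6% in 9. These limits take the denominator as exactly 17 or 9; if some children are replaced, the number with a started infusion would be larger and the limits slightly lower. It would be worth correcting before data accrue.

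**What to change.** Amend the primary safety endpoint under Outcomes, and its analysis under Statistical methods, as follows.

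- **Primary result:** the number and proportion of children with at least one moderate-or-worse adverse event within 52 weeks, with an exact 95% confidence interval.
- **Causality:** count events definitely, probably or possibly related to the product, to the infusion procedure or to bead retrieval, shown separately and combined.
- **Denominator:** all children in whom an infusion was started, including any who are replaced or have incomplete data.
- **Beside it:** the same table regardless of causality, with the count of occurrences as supplementary information.
- **Wording of the conclusion:** state the largest risk that the achieved number of children can exclude.

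The cost is a protocol wording change (this is a primary endpoint, so analysis-plan text alone is not enough), one table, and one field on the adverse event form for relation to procedure, unless the form, which is not shown, already has it. Events, grades and causality are already collected, and the article states that recruitment had not begun. The drawback is a headline safety figure that will look less favourable. For children whose beads are washed out at transplantation, separating retrieval harm from transplant harm will need judgement, which is a further reason to show the all-cause table.

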#### Secondary objective

To establish proof of concept of the transplantation of microbeads made from the optimum combination of modified alginate, MSCs and hepatocytes. To inform the sample size and confidence intervals to design a larger randomized clinical trial.

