### Trial design

This is an, open-label, single-arm, single centre study. A Simon’s two-stage design for a one-sample exact test will be used. We assume a one-year survival rate of 0.20 or less under the null hypothesis, and 0.5 or more under the alternative, with 80% power and 5% type I error rate.

The primary outcome survival measure is set at 24-weeks. Although response to treatment is anticipated to be within the first 4–6 weeks, short to medium term morbidity in children who have been critically unwell in the Pediatric Intensive Care Unit (PICU), Neonatal Intensive Care Unit (NICU) or High Dependency Unit (HDU), is best determined at a longer time point such as 24 weeks. This way almost all possible later deaths due to the acute liver failure (or early post-transplant deaths) will be effectively captured.

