#### Sample size

Simon’s two-stage design for a one-sample exact test was estimated, assuming a one-year survival rate of 0.20 or less under the null hypothesis, and 0.5 or more under the alternative, with 80% power and 5% type I error rate. A total of 17 patients will be recruited into the study (at the end of stages 1 and 2). 9 patients will be recruited into the study in the first stage. Once 9 patients have completed their 24 weeks visit, the study will stop for futility if only 2 or fewer patients have survived with the native liver. At the end of the second stage, if 7 or more patients out of the 17 enrolled have survived with native liver at 24 weeks post HMB002 treatment, this will demonstrate proof of concept. DSMB approval is required for progression to Stage 2, where the trial will continue to recruit a further 8 patients. this will be extended to 17 patients as part of the Simon two stage design if there is evidence to support continuation. A long-term follow-up period will be used to monitor safety over a 10-year period post investigational medicinal product (IMP) infusion.

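### The planned 24-week native-liver survival estimate and its 95% interval match neither the count that decides proof of concept nor the level of that test

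*Protocol article*

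**What the plan says.** **Decision rule (Protocol article, Sample size).** The trial uses Simon's exact two-stage test. The null rate is given by "assuming a one-year survival rate of 0.20 or less under the null hypothesis". The target rate is at least 0.5, the type I error is set at 5% and the power at 80%. Nine patients enter stage 1, and the trial stops if two or fewer are alive with their native liver at 24 weeks. Proof of concept is shown "if 7 or more patients out of the 17 enrolled have survived with native liver at 24 weeks post HMB002 treatment".

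**Reported result (Protocol article, Statistical methods, primary endpoints).** "Survival with native liver at 24 weeks post treatment and 95% confidence interval will be reported". The same sentence fixes the estimator: one minus the cumulative incidence of dying with the native liver in place, with transplantation as the competing event. The 52-week secondary endpoint uses the same formula. No interval construction is named.

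**Use of the result (Protocol article, Secondary objective).** "To inform the sample size and confidence intervals to design a larger randomized clinical trial".

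**The concern.** The same primary endpoint is handled in two ways that do not agree.

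- **Estimator.** The decision counts patients alive with their own liver, so a transplant is a failure. The reported figure subtracts only deaths before transplant, so a transplanted patient is not a failure.
- **Level.** A null of 0.20 or less with an upper-tail success rule is in effect a one-sided 5% test. A two-sided 95% interval corresponds to one-sided 2.5%.

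The trial could declare proof of concept on one quantity and publish another under the same name. It could also publish an interval that fails to exclude the null it has just rejected. Because the estimate and interval are meant to feed the design of a randomised trial, the error would carry forward.

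**Working it through.** **Inputs.** From Sample size: n1 = 9, stop at 2 or fewer; N = 17, success at 7 or more; p0 = 0.20; p1 = 0.50; type I error 5%; power 80%. The rates are worded as one-year survival, but I apply them to the 24-week count, as the rule does. Under Methods for additional analyses, only patients with complete data are analysed, so I assume no censoring before 24 weeks.

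**1. Reproduce the design.** P(success; p) = Σ over x = 3 to 9 of P(X1 = x) × P(X2 ≥ 7 − x), with X1 ~ Bin(9, p) and X2 ~ Bin(8, p).

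- p = 0.20: 0.0341. Probability of early stopping: 0.738.
- p = 0.50: 0.8057.

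The stated 5% and 80% are met. This is the minimax Simon design for these inputs.

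**2. The estimator as written.** Without censoring, the cumulative incidence of death before transplant is d/17, where d is the number of such deaths. The reported figure is therefore 1 − d/17. With 7 native-liver survivors, deaths and transplants sum to 10:

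| Deaths | Transplants | Native-liver survivors | Reported as written |
|---|---|---|---|
| 10 | 0 | 7/17 = 41.2% | 7/17 = 41.2% |
| 5 | 5 | 7/17 = 41.2% | 12/17 = 70.6% (exact 95% about 44.0 to 89.7) |
| 2 | 8 | 7/17 = 41.2% | 15/17 = 88.2% (63.6 to 98.5) |
| 0 | 10 | 7/17 = 41.2% | 17/17 = 100% |

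The figure can be high in a trial that fails the rule. With 4 native-liver survivors, 3 deaths and 10 transplants it is 1 − 3/17 = 82.4%, against 4/17 = 23.5% alive with native liver.

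**3. The level, for the count itself.** At 7/17 = 0.4118:

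- Wald 95%: SE = √(0.4118 × 0.5882 / 17) = 0.1194; 0.4118 ± 1.96 × 0.1194 gives 17.8% to 64.6%. Includes 20%.
- Exact (Clopper-Pearson) 95%: 18.4% to 67.1%. Includes 20%.
- Log-log on survival 95%: 18.6% to 62.6%. Includes 20%.
- Two-stage exact 95%: the lower limit solves P(success; p) = 0.025, and the upper limit sets the probability of 8 or more to 0.975. This gives 18.8% to 67.7%. Includes 20%.
- Wilson 21.6% to 64.0%, Agresti-Coull 21.6% to 64.1%, Jeffreys 20.7% to 64.4%, log 23.3% to 72.7%, log-log on cumulative incidence 22.2% to 67.5%. All exclude 20%.
- Two-stage exact **90%**: 21.6% to 64.1%. Clopper-Pearson 90%: 21.2% to 63.6%. Both exclude 20%.

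The two-stage p-value at 7/17 is 0.0341, which lies between 0.025 and 0.05. The two-stage exact interval must therefore include 20% at the 95% level and exclude it at 90%. At 8/17 the p-value is 0.0105, and every method tried excludes 20% at 95%.

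**4. How often exactly 7 occurs.** The number of ways to reach 7 after passing stage 1 is Σ over x = 3 to 7 of C(9, x)C(8, 7 − x) = 5880 + 7056 + 3528 + 672 + 36 = 17172. So P(7; p) = 17172 p⁷(1 − p)¹⁰.

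- p = 0.50: 0.131, or 0.131/0.806 = 16% of successes.
- p = 0.20: 0.0236, or 0.0236/0.0341 = 69% of successes.

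**5. Effect of the two-stage adjustment on the estimate.** UMVUE at 7/17 = Σ C(8, x − 1)C(8, 7 − x) / 17172 = 7532/17172 = 43.9%, against 41.2%. The bias of the raw proportion is −2.2 points at p = 0.20, −2.8 at 0.35 and −1.3 at 0.50.

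**The case against.** The best defence is that the count alone decides and the interval is only reported. A one-sided 5% go rule beside a conventional 95% interval is common in early-phase work, and the method of interval is often left to the analysis plan. This stands as far as it goes: the interval is not a decision criterion, the rule keeps its error rates, and the level mismatch alone would be a matter of interpretation.

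It could also be said that the cumulative-incidence wording is loose shorthand for survival free of both death and transplant. If both cumulative incidences were subtracted, the result would be 7/17. But the text subtracts death only, and Methods for additional analyses likewise treats transplantation as a competing risk for time to death. The formula is stated, so it is not a detail left open.

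Four stronger readings are tempting and are not supported:

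- **That any 95% interval at 7/17 contains 20%.** Wilson, Agresti-Coull, Jeffreys and others exclude it, and the protocol names no method.
- **That decision and interval conflict in general.** Only the count 7 is affected.
- **That ignoring the two-stage design causes the conflict or seriously biases the result.** The two-stage 95% interval still includes 20%, and the bias is at most about 3 points. Silence on an adjusted estimator is not an error here.
- **That the interval will under-cover.** Coverage of 85.5% at p = 0.20 and 87.9% at p = 0.50 holds for a Wald interval, which the protocol does not specify. Wald covers 94.7% at p = 0.30. Over the same design, Clopper-Pearson covers 98.9% and 94.9% at p = 0.20 and 0.50, and Wilson 96.6% and 94.9%.

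**Conclusion.** The point holds in two parts of unequal weight.

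**Estimator (the main part).** The stated analysis does not estimate the quantity that the Simon rule tests. At the success threshold the reported figure can lie anywhere from 41.2% to 100%, depending only on how the 10 failures divide between death and transplant. The documents do not predict that division, so the table shows a range and not an expected error. The result assumes complete 24-week follow-up.

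**Level (the lesser part).** At exactly 7/17 it depends on an unnamed method whether the 95% interval agrees with the decision. If readers required the exact 95% interval to exclude 20%, the rule would in effect become 8/17: type I error 0.0105 and power 0.675, instead of 0.0341 and 0.806. One-sidedness is inferred from the form of the hypotheses, since the protocol does not state it.

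Neither part invalidates the design or the decision rule. The harm is to what is published and to what is carried into the randomised trial.

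**What to change.** - Report the 24-week primary endpoint as the binomial proportion alive with native liver, counting death or transplant as failure. Correct the 52-week endpoint's formula in the same way.
- Give an exact interval that respects the two-stage design, at 90% to match the one-sided 5% test. At 7/17 this is 21.6% to 64.1%.
- If a 95% interval is also wanted, name the method and label it descriptive.
- Show the cumulative incidences of death and of transplant side by side, as supportive displays only.
- Optionally add the UMVUE (43.9% at 7/17).

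The cost is a change of wording in the protocol or analysis plan and a few lines of code. The article says that recruitment has not begun, so the change can be made before any data exist. The downside is one extra interval to explain.
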